### 1. Bacterial vaginosis

Prevalence among pregnant and postnatal women. The prevalence of BV and other forms of disturbance of vaginal flora are common among Malawian women. This is consistent with reports from other African countries (2,3). As shown in Table 3, among two large cohorts of pregnant women screened in 1990 and 1993, respectively, only 11% of women had normal vaginal flora, about 59% had a mild to moderate disturbance and 30% had a severe disturbance (i.e., BV) (34). We used clinical criteria to define BV. Table 4 shows that BV, trichomoniasis and candidiasis each accounted for rates of approximately 14 to 16 per 100 person-visits among women we followed postnatally in Malawi (24).

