**Table 3. Prevalence of disturbances of vaginal flora among pregnant women surveyed in 1990 and 1993, Blantyre, Malawi.**

| Disturbance of vaginal flora*   | N=9126 (1990/1993) |
|---------------------------------|--------------------|
| Normal                          | 10.7%              |
| Mild (1 criterion)              | 38.3%              |
| Moderate (2 criteria)           | 21.0%              |
| Severe (BV: 3 or more criteria) | 30.0%              |

\* Based on the following clinical criteria: vaginal pH>4.5, vaginal discharge, presence of clue cells $\geq$ 20%, and a positive amine (Whiff) test.

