**Table 4. Frequency of bacterial vaginosis and STDs among postpartum women in Blantyre.**

| Disease             | Person visits | Event-visits | Rate/100 person visits | 95% CI      |
|---------------------|---------------|--------------|------------------------|-------------|
| Bacterial vaginosis | 4479          | 736          | 16.43                  | 15.20-17.58 |
| Gonorrhea           | 4130          | 44           | 1.07                   | 0.75-1.39   |
| Trichomoniasis      | 4015          | 567          | 14.12                  | 12.70-15.50 |
| Syphilis            | 4905          | 128          | 2.61                   | 1.82-3.40   |
| Candidiasis         | 4012          | 561          | 13.98                  | 12.78-15.14 |

Association of BV with adverse reproductive outcomes. There were consistent associations between disturbances of vaginal flora and low birth weight, reduced mean birth weight, preterm birth (<37 weeks gestation) and higher neonatal mortality. Table 5 shows that there was a statistically significant trend of associations between disturbance of vaginal flora and these outcomes: adverse outcomes were lowest among women with normal vaginal flora and highest among women with BV - severe disturbance.

**Table 5. Association of disturbance of vaginal flora (based on clinical criteria) with adverse reproductive outcomes among women enrolled during pregnancy in 1990.**

|                                | Normal
N=124 | Mild
N=441 | Moderate
N=315 | Severe
N=473 | P-value* |
|--------------------------------|-----------------|---------------|-------------------|-----------------|----------|
| Mean birth weight (g)          | 2977            | 2948          | 2908              | 2820            | 0.001    |
| LBW** (<2,500g) %              | 9.7             | 14.3          | 18.1              | 20.3            | <0.003   |
| Gestational age <37wks %       | 14.5            | 17.0          | 18.8              | 23.5            | <0.005   |
| Neonatal deaths*** %           | 3.1(N=97)       | 4.2(N=335)    | 8.0(N=251)        | 8.0(N=324)      | 0.012    |
| Adverse outcomes
combined ¶ | 19.2            | 23.9          | 27.6              | 30.4            | 0.003    |

\*  $X^2$  trend for LBW, gestational age <37 weeks and neonatal deaths; ANOVA for mean birth weight comparisons.

\*\* Low birth weight.

\*\*\* Figures in brackets are actual denominators.

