### D. 4. STATISTICAL CONSIDERATIONS

**Primary endpoints.** a) Incidence/Prevalence of BV at cross-sectional visits; b) Portion of pregnancies lost during the first 14 weeks of gestation; c) Incidence of adverse reactions to the product (portion of subjects having adverse reactions); and d) Rates of participation in study, adherence to treatment, and subsequent dropout.

**Sample size and power.** The following design specifications will apply: number of treatment groups: 2; follow-up period: approximately one year; hypotheses will be tested using a one-sided type 1 error of  $\alpha=0.05$ . Unless stated otherwise, powers are obtained based on Fisher's exact test for comparisons of proportions in two groups using software developed by Dupont and Plummer (56).

We will recruit 1664 women of whom 832 will be HIV infected and 832 will be uninfected. In each group of women, 416 will be randomized to treatment arm and 416 to placebo arm. Based on previous experience in Malawi, losses due to dropouts and non-compliance will be less than 10% per year. Thus at least 375 women in each arm will return to each study visit during the first year.

**Specific aim 1.** Power estimates for specific aim 1 is shown in Tables 11. In previous studies from Malawi, cross sectional prevalence of BV among untreated women was 30% and that of any vaginal disturbance was 89% (24).

**Table 11. Estimated power for specific aim 1 (comparing BV at each visit during the first study year assuming at least 375 evaluable study subjects in each group).**

| Normative rate
in untreated women | Reduction from intervention |            |
|----------------------------------------------|------------------------------------|------------|
|                                              | 33%                         | 50% |
| 0.30                                         | .87                                | ~1.00      |
| 0.89                                         | ~1.00                              | ~1.00      |

Thus there will be 0.87 and almost 1.00 power to detect 33% reductions in cross sectional visit prevalence of BV (normative rate 0.30 in untreated subjects) and any vaginal flora disturbance (normative rate .89 in untreated subjects).

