##### 3.1.3 Intervention:

Women (both HIV positive and negative) will be randomized at the three months postnatal visit and issued the intervention (either metronidazole gel or placebo). We will use metronidazole vaginal gel, 0.75% MetroGel-Vaginal (3M Pharmaceuticals) in this study. The product is used intravaginally once a day at bedtime for five consecutive nights. The placebo is similar to the active product but without the active ingredient.

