#### 12.3.1 Instructions for using the allocation study ID's

##### By Whom

Study coordinator (as the rest of the study investigators and workers, the study coordinator is completely blinded about the treatment assignment).

Procedure

1. Assign these Lists to the five Study Clinics as shown in section 12.3. above
2. Each woman enrolling in the study will be sequentially assigned the next available ID in each clinic.

12.4 Sample size and analysis plan12.4.1 Sample size and power:

The following design specifications will apply: number of treatment groups: 2; follow-up period: approximately one year; hypotheses will be tested using a one-sided type 1 error of  $\alpha=0.05$ . Unless stated otherwise, powers are obtained based on Fisher's exact test for comparisons of proportions in two groups.

We will recruit 1664 women of whom 832 will be HIV infected and 832 will be uninfected. In each group of women, 416 will be randomized to treatment arm and 416 to placebo arm. Based on previous experience in Malawi, losses due to dropouts and non-compliance will be less than 10% per year. Thus at least 375 women in each arm will return to each study visit during the first year.

Primary endpoint: effect of treatment on BV incidence. Power estimates for this primary endpoint are shown in Tables 12.1. In previous studies from Malawi, cross sectional prevalence of BV among untreated women was 30% and that of any vaginal disturbance was 89%.

**Table 12.1. Estimated power for specific aim 1 (comparing BV at each visit during the first study year assuming at least 375 evaluable study subjects in each group).**

| Normative rate
in untreated women | Reduction from intervention |       |
|--------------------------------------|------------------------------------|-------|
|                                      | 33%                                | 50%   |
| 0.30                                 | .87                         | ~1.00 |
| 0.89                                 | ~1.00                       | ~1.00 |

Thus there will be **0.87** and almost **1.00** power to detect 33% reductions in cross sectional visit prevalence of BV (normative rate 0.30 in untreated subjects) and any vaginal flora disturbance (normative rate .89 in untreated subjects).

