### 13.0 ADDENDUMS

#### 13.1 Study population

Women who have been screened for HIV in other studies such as the HIVNET 016A condom promotion and Mastitis studies are eligible for enrollment. Likewise, women of reproductive age who are sexually active (e.g., women attending family planning clinics, postnatal and under-five clinics) are also eligible as long as they agree to be HIV tested. All prospective participants should not be pregnant. This modification opens enrollment to all women who satisfy inclusion criteria. The study is not restricted to postnatal women.

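### The single-visit BV power of .87 rests on a 30% prevalence documented only in pregnant women; at the protocol's postpartum rate of 16.4% it is .54 (one-sided 0.025) or .66 (one-sided 0.05), a shortfall clearest for HIV-uninfected women

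*Protocol*

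**What the plan says.** Section 12.4.1 gives the basis for the BV power: in previous Malawian studies "cross sectional prevalence of BV among untreated women was 30" per cent, and any vaginal disturbance was 89%. Table 12.1 then gives .87 power for a 33% reduction and about 1.00 for a 50% reduction, with at least 375 evaluable women per group at each visit. The 375 is the number per arm within one HIV group (416 randomized, under 10% lost). Section D.4 and Table 11 say the same and cite reference 24. The stated test is Fisher's exact test at one-sided 0.05.

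The origin of the 30% and 89% is in section C.1 and Table 3. C.1 reports that "among two large cohorts of pregnant women screened in 1990 and 1993, respectively, only 11% of women had normal vaginal flora", with 30% having BV. Table 3 is headed "Prevalence of disturbances of vaginal flora among pregnant women surveyed in 1990 and 1993, Blantyre, Malawi". C.1 cites reference 34 for these figures, not reference 24.

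The same paragraph of C.1 also gives a postnatal figure, citing reference 24: "BV, trichomoniasis and candidiasis each accounted for rates of approximately 14 to 16 per 100 person-visits among women we followed postnatally in Malawi". Table 4, "Frequency of bacterial vaginosis and STDs among postpartum women in Blantyre", gives BV at 736 of 4479 person-visits, 16.43 per 100 (95% CI 15.20-17.58).

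On the trial population, section 3.1.3 says women "will be randomized at the three months postnatal visit and issued the intervention". Section 3.1.6 excludes women pregnant at enrollment. Addendum 13.1 opens the trial to other sexually active women but keeps one condition: "All prospective participants should not be pregnant".

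**The concern.** The control rate for the first primary endpoint is taken from a group that the trial excludes, although the protocol holds a figure for a group much closer to its own. The two rates differ by almost a factor of two.

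The measures are comparable. The footnote to 12.6 says that the endpoint called incidence is really cross-sectional prevalence, mixing new and continuing cases. A rate per 100 person-visits is that kind of quantity.

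For a fixed relative reduction, a lower control rate means a smaller absolute difference and lower power. If the true rate is near 16%, a null single-visit comparison in one HIV group could be read as a well-powered negative when it is not. One 30% figure also serves both HIV groups, although the protocol's own Table 6 shows that BV and HIV are strongly associated.

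**Working it through.** **Inputs.** n = 375 per arm (12.4.1; 416 × 0.9 = 374.4). Reduction 33%, so the treated rate is 0.67 × control. Control rate 0.30 (12.4.1) or 736/4479 = 0.1643 (Table 4). Alpha is one-sided 0.05 as stated in 12.4.1, or one-sided 0.025 as named for the final analysis in the monitoring paragraph of D.4.

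**Method.** Exact unconditional power of Fisher's test: sum Bin(x₁; 375, p₁) × Bin(x₂; 375, p₂) over all pairs (x₁, x₂) whose one-sided hypergeometric tail probability is at most alpha.

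**Reproducing the plan's figure.** At 0.30 against 0.201, power is .865 at one-sided 0.025 (.872 if the reduction is exactly one third) and .921 at one-sided 0.05. So .87 is reproduced at 0.025 and not at the stated 0.05. This conflict is a separate matter, so both levels are shown below.

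**Changing only the control rate (375 per arm).**

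| Control rate | Reduction | One-sided 0.025 | One-sided 0.05 |
|---|---|---|---|
| 30% | 33% | .87 | .92 |
| 25% | 33% | .77 | .86 |
| 20% | 33% | .65 | .76 |
| 16.43% | 33% | .54 | .66 |
| 16.43% | 50% | .92 | .96 |

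Over the Table 4 confidence limits (15.20% to 17.58%), power for a 33% reduction is .50-.58 at 0.025 and .62-.70 at 0.05. At 16.43% and 0.025, a reduction of about 47% is needed to reach roughly .87.

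**By HIV status.** Table 6 gives HIV prevalence overall and among women with BV. Assuming 30% BV overall in both survey years, Bayes' rule gives BV in pregnancy as follows:

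- 1990: HIV-infected 0.308 × 0.30 / 0.225 = 41%; uninfected 0.692 × 0.30 / 0.775 = 27%; ratio 1.53.
- 1993: HIV-infected 0.439 × 0.30 / 0.300 = 44%; uninfected 0.561 × 0.30 / 0.700 = 24%; ratio 1.83.

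Even in pregnancy, then, 30% is above the implied rate for uninfected women. If Table 4 is taken as an HIV-uninfected rate and these ratios are assumed to hold postnatally, the HIV-infected rate is 16.43 × 1.53 to 16.43 × 1.83, or about 25-30%. Power for a 33% reduction is then about .77-.87 at 0.025 and .86-.92 at 0.05.

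**Repeated-visit analysis.** With four quarterly post-treatment visits, a common effect and exchangeable within-woman correlation ρ (assumed 0.2 to 0.5), the effective n per arm is 375 × 4 / (1 + 3ρ). That is 938 at ρ = 0.2 and 600 at ρ = 0.5. At 16.43% against 11.0% and one-sided 0.025, the normal approximation gives power of .93 and .78.

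**The case against.** The strongest objection is that Table 4 does not speak for both HIV groups. C.1 cites reference 24 for it, and the postnatal cohort that C.1 describes from that reference is 1,169 HIV-seronegative women. BV person-visits of 4479/1169 = 3.8 per woman fit that cohort. This is an inference, because Table 4 does not state HIV status, but it is plausible. Half the trial is HIV-infected, and for those women 30% may be close to right. This stands.

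Second, addendum 13.1 states that the study is not restricted to postnatal women. The protocol gives no Malawian BV rate for family-planning attendees and similar women, and B.1 mentions prevalences above 50% in African women. So 16.4% is not established as the rate for everyone enrolled, nor is 30% established as an upper limit. This also stands, but it gives no support to a pregnancy rate.

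Third, a 50% reduction remains well powered. That is true, but the headline claim is for 33%.

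A reader might go further and infer that the trial's primary BV test has nearly even odds of missing a 33% reduction in either HIV group. The documents do not support that. The near-even figure needs one-sided 0.025; at the stated 0.05 the chance of a miss is 34%. It also applies a rate not split by HIV status to both groups. And no passage names a single visit as the primary test: Tables 11 and 12.1 power each visit, but 12.6 also plans a comparison across all post-intervention visits.

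**Conclusion.** The concern holds in a limited form. The per-visit, per-stratum power of .87 depends on a prevalence that the protocol documents only in pregnant women. At its only non-pregnant rate, power for a 33% reduction is .54 at one-sided 0.025 or .66 at one-sided 0.05. Under neither alpha is .87, or even .80, reached.

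The shortfall is clearest for HIV-uninfected women. For HIV-infected women the protocol gives no postnatal rate, and on the assumptions above power could be anywhere from somewhat short of the claim to in line with it. The .87 is correct arithmetic from its input at one-sided 0.025, so the fault is in the planning assumption and its labelling. It does not show that the trial is too small for its BV aim: the planned repeated-visit analysis recovers about .78-.93 per HIV group at 16.4%, given the assumed correlations.

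**What to change.** In 12.4.1 and D.4:

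- Label 30% and 89% as rates in pregnant women, and reconcile the citation, since D.4 and C.1 credit them to different references.
- In Tables 11 and 12.1, add rows for control rates of 0.16, 0.20 and 0.25 beside 0.30, all at one named alpha.
- State that the .87 for a 33% reduction at a single visit does not hold at the postnatal rate, mainly for HIV-uninfected women, and that no postnatal rate for HIV-infected women is given.
- Rest the main power statement on the repeated-visit GEE in 12.6, naming the visits counted and the assumed within-woman correlation.

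The cost is a few table rows and sentences and a less favourable single-visit figure. No extra women are needed, and no new analysis has to be added.

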For some analyses we will pool repeated measurements from the same individual over multiple study visits. For example, occurrence of BV across all post-intervention study visits will be compared between study groups. For these analyses, generalized estimation equation models, which use an individual as cluster unit, will be fit to obtain robust covariance. For binary outcomes, a logit link will be used.

Data monitoring and reporting. This trial will be monitored by a Data and Safety Monitoring Board (DSMB). Formal interim analyses of efficacy of the intervention, based on the primary endpoints, will then be performed at approximately six month intervals during the projected study duration. Recommendations for early termination of positive or negative results will be guided by the symmetric group sequential O'Brien-Fleming Boundary (58). The O'Brien-Fleming design allows for early termination if extreme initial results are seen, while essentially allowing employment of the standard single stage one-sided 0.025-level test statistic at the final analysis if it is reached. This enables one to maintain the power of the single-stage design in the presence of interim monitoring without having to increase the maximum sample size. As has been the plan for other clinical trials conducted by our research team in Malawi, we will arrange for regular dissemination of information.

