### 12.2 Endpoints

#### 12.2.1 Primary endpoints

- Incidence/Prevalence of BV at cross-sectional visits;
- Rate of conception and portion of pregnancies lost during the first 14 weeks of gestation;
- Incidence of adverse reactions to the product (portion of subjects having adverse reactions).

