### 12.6 Data analysis.

Analyses will be done using an intention to treat approach. Separate analyses for HIV infected and uninfected women will be performed and the effect of the intervention on outcomes in these two groups will be compared. The effect of the intervention will be based on comparing incidence of BV and portion of pregnancy losses between treated and untreated (control) subjects.

Multiple hypotheses will be tested in this study, requiring a diverse array of analytical methods to compare the treatment and control arms. Descriptive comparisons will be made between the two study groups to identify potential confounding variables which could bias hypothesis testing through direct comparisons. When possible, as differences are noted, multivariate adjustment methods will be used to minimize the effect of confounders on testing the hypotheses. Continuous variables will be tested for skewness, kurtosis and outliers which could cause imprecision in standard asymptotic statistical methods. When such conditions occur, transformations such as logarithms, dichotomization or Winsorizing will be used, or nonparametric statistical methods will be implemented. For the statistical tests described below, both P-values and confidence intervals will be calculated for the parameters of interest.

---

 Although we use the term incidence in the text, it is more accurate to define this measure as cross-sectional prevalence because the number of BV cases during a 3 month interval are a combination of new and continuing cases (due to incomplete cure and recurrences).

Most outcomes of interest (e.g., presence of BV) are uncensored binary or categorical events. These include demographic and specific behavioral factors, etc. Contingency (n x 2) tables will be used to compare these events between the two study arms. Adjustment for covariates will be made with logistic regression. Comparison of binary events between two time-points within the same group will be done using methods that match on the same individual such as discordant pairs or conditional logistic regression. In other outcomes of interest which are continuous comparison of mean values will be made using t-tests. Adjustments for covariates will be performed through linear regressions. Comparisons of continuous covariates for the same individuals in a group over different time periods will be made using paired z-tests and linear regressions on differences of values.

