Some outcomes will be censored binary events. Standard survival analysis techniques such as Kaplan-Meier curves and Poisson regression will be used to directly compare outcome in both groups. These methods can also compare incidence rates within the same group over different time periods. Multivariate analogues that utilize covariates (proportional hazards models and Poisson regression) will adjust these comparisons for other covariates.

For some analyses we will pool repeated measurements from the same individual over multiple study visits. For example, occurrence of BV across all post-intervention study visits will be compared between study groups. For these analyses, generalized estimation equation models, which use an individual as cluster unit, will be fit to obtain robust covariance. For binary outcomes, a logit link will be used.

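### The primary BV endpoint is a set of per-visit tests in two HIV strata at an unsplit one-sided alpha, with no single test named to decide success

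*Protocol*

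**What the plan says.** Section 12.2.1 of the manual gives the first primary endpoint as "Incidence/Prevalence of BV at cross-sectional visits". Table 12.1 in Section 12.4.1 (Table 11 in Section D.4 of the research plan) powers it by "comparing BV at each visit during the first study year", with 375 evaluable women per arm. That is 416 per arm within one HIV stratum, less 10%.

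On alpha, Section 12.4.1 says that "hypotheses will be tested using a one-sided type 1 error of" 0.05, with no division among visits, strata or endpoints. The monitoring paragraph of Section D.4 instead refers to the "standard single stage one-sided 0.025-level test statistic at the final analysis".

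On the analysis, Section 12.6 says "Separate analyses for HIV infected and uninfected women will be performed", and the same sentence adds that the intervention effects in the two groups will be compared. It acknowledges that many hypotheses will be tested. It gives, as an example of what some analyses will do, a GEE model in which "occurrence of BV across all post-intervention study visits will be compared between study groups".

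The two lists of primary endpoints differ. Section D.4 includes "Rates of participation in study, adherence to treatment, and subsequent dropout" among the primary endpoints, while Section 12.2.2 of the manual makes it secondary. Section 12.2.1 adds the rate of conception, which Section D.4 does not list.

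**The concern.** By Section 3.2.1, BV is measured after randomisation at four quarterly visits (V2 to V5) and four test-of-cure visits (V1.9 to V4.9). With separate analyses in two HIV strata, the primary endpoint as worded covers 8 comparisons, or 16 with the test-of-cure visits, each at full alpha. Nothing says which of them must be significant for the trial to have shown an effect on BV.

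Two things are at stake. First, a favourable result at one visit in one stratum could be reported as a primary success, with an error rate well above the nominal level. Second, the claim would rest on the least informative comparison available, one visit in one stratum, although the trial collects all visits in both strata and already describes a model that uses them together.

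**Working it through.** **1. The plan's own figure.** Inputs from Section 12.4.1: 375 per arm, BV 0.30 in controls, a 33% reduction (0.30 to 0.201, or 0.200 for exactly one third), and "powers are obtained based on Fisher's exact test for comparisons of proportions in two groups". Exact power of the one-sided Fisher test:

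- at 0.05: 0.921 to 0.926
- at 0.025: 0.865 to 0.872

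The printed 0.87 is reproduced at 0.025, not at the printed 0.05. Table 12 in Section D.4 (300 per arm) behaves the same way: at 0.025 I get 0.54, 0.92, 0.78 and 0.99 against the printed 0.54, 0.91, 0.78 and 0.99. Both alphas are therefore carried below.

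**2. False-positive chance for BV alone, V2 to V5 in two strata.** Under the null, with eight independent tests at 0.05: 1 − 0.95^8 = 33.7%.

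Repeat tests on the same women are correlated. The protocol gives no correlation, so I assume an equal between-visit correlation ρ of 0.2 to 0.5. Let S be the chance that none of the four visits in one stratum is significant (simulated multivariate normal). The strata are independent, so the chance of at least one false positive is 1 − S².

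| ρ | S at 0.05 | 1 − S² | S at 0.025 | 1 − S² |
|---|---|---|---|---|
| 0.2 | 0.828 | 31% | 0.910 | 17% |
| 0.3 | 0.836 | 30% | 0.912 | 17% |
| 0.5 | 0.856 | 27% | 0.922 | 15% |

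Fisher's test is conservative: with 375 per arm and BV 0.30 its actual size is 0.043 at nominal 0.05 and 0.021 at nominal 0.025. Simulated binary data with Fisher tests give about 24-28% and 13-15%.

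**3. Wider counts, at one-sided 0.05.**

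- Adding the four test-of-cure visits (BV only, 8 visits in 2 strata): about 39-50%.
- Adding conception and pregnancy loss in each stratum to the eight BV tests (four more tests, taken as independent): 1 − S² becomes 1 − S² × 0.95^4, or about 40-44%.

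**4. Power, one visit against pooled visits.** All figures use the normal approximation, one-sided 0.025 and a 33% reduction held constant over V2 to V5:

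Power = Φ[(d − z√(2p̄(1−p̄)/n)) / √((p1(1−p1)+p2(1−p2))/n)], where d = p1 − p2 and p̄ is their mean. For pooled visits n is replaced by 375 × 4/(1 + 3ρ), which is 937.5 at ρ = 0.2 and 600 at ρ = 0.5; it is doubled for both strata.

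- Design value, p1 = 0.30, p2 = 0.201, one visit, one stratum: (0.099 − 1.96 × 0.03164)/0.03144 = 1.18, power 0.88. Pooled visits, one stratum: 0.98 or more.
- Postpartum value, p1 = 0.1643 (Table 4: 736/4479 person-visits), p2 = 0.1101, one visit, one stratum: (0.0542 − 1.96 × 0.02513)/0.02505 = 0.20, power 0.58. Pooled visits, one stratum: 0.78 (ρ = 0.5) to 0.93 (ρ = 0.2). Both strata: 0.97 or more.

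**The case against.** **No rule says that any significant test wins.** This is correct. A reader might infer that the plan has a stated 30% error rate. It does not: the figure follows from an any-test reading that the document neither adopts nor excludes. What stands is that nothing in the text prevents such a claim.

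**The smaller alpha may be the real one.** Section D.4 refers to 0.025 and the power tables reproduce only there. The BV figure is then 15-17%, which is still several times the nominal level.

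**Testing order can be left to a statistical analysis plan.** In general it can. Here the protocol itself fixes the endpoint wording, the per-visit comparison, the separate strata and the undivided alpha, so a later plan would have to depart from this text.

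**Stratum-specific results are a design choice.** The aims name both groups of women and each stratum is sized at 832. That supports keeping them, if necessary as primary with a split alpha; it does not support testing each visit in each stratum at full alpha. A reader might also infer that no comparison across the strata is planned. Section 12.6 does plan to compare the effects in the two groups, and its GEE example is not confined to one stratum. What is missing is a designated overall test.

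**The per-visit test is adequately powered.** At the design's 30% BV it is: 0.88 against 0.98 or more is a modest gain, so a reader should not conclude that the per-visit test is weak under the plan's own assumptions. The gap is large only at a lower rate such as the 16.4 per 100 person-visits of Table 4.

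**Not every primary endpoint is an efficacy claim.** Adverse reactions are a safety endpoint and adherence is primary only in the research plan, so neither is counted above.

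**Conclusion.** The point holds for the structure of the BV endpoint: several visits, two strata, one undivided alpha and no deciding test. For BV alone at V2 to V5, the chance of at least one false positive is about 27-31% at one-sided 0.05 and about 15-17% at one-sided 0.025, somewhat lower with Fisher's test. The size rests on two assumptions that the document does not state: a between-visit correlation of 0.2 to 0.5, and reading any significant test as success. It does not include the other primary endpoints or the test-of-cure visits, which would raise it.

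The case for making the pooled model primary rests first on error control. The gain in power is a second reason, small at the design rate and substantial at the postpartum rate in Table 4, provided the effect is constant over visits. This should be corrected; it does not invalidate the design.

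**What to change.** In Sections 12.2.1 and 12.6, state:

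- The primary BV analysis is one GEE logistic model of BV at V2 to V5 in all randomised women, with HIV stratum in the model, tested once at one stated alpha. Reconcile the 0.05 of Section 12.4.1 with the 0.025 of Section D.4, and make the power tables match.
- HIV-specific effects, the comparison of effects between the HIV groups that Section 12.6 already plans, single visits and test-of-cure visits are secondary.
- If stratum-specific claims must stay primary, use one GEE test per stratum with alpha divided between the two. With 0.025 split as 0.0125 each (z = 2.24), 30% BV, a 33% reduction and ρ = 0.5, the formula above gives (0.099 − 2.24 × 0.02502)/0.02485 = 1.73, or power of about 0.96 per stratum.
- Make the primary-endpoint lists in Section D.4 and Sections 12.2.1 and 12.2.2 identical.

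The cost is wording only: no extra women, visits or samples, and the randomisation lists are already separate by HIV status. There are two small downsides. A joint test assumes effects in the same direction in both strata, which the planned comparison of effects can check. V2 to V5 fall three months after each course, and Section D.3.a cites 50%-70% recurrence by then, so the pooled effect may be smaller than the effect at test of cure. The text should say that this was chosen deliberately.
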